## DEFINITION OF UNANTICIPATED ADVERSE DEVICE EFFECT

Per 21 CFR 812.3(s), an unanticipated adverse device effect is defined as “any serious adverse effect on health or safety or any life-threatening problem or death caused by, or associated with, a device, if that effect, problem, or death was not previously identified in nature, severity, or degree of incidence in the investigational plan or application (including a supplementary plan or application), or any other unanticipated serious problem associated with a device that relates to the rights, safety, or welfare of subjects.”

## RECORDING ADVERSE EVENTS AND SERIOUS ADVERSE EVENTS

When an AE, SAE, or UADE occurs, the investigator will be responsible for reviewing all documentation (e.g., hospital progress notes, laboratory, and diagnostic reports) relative to the event(s). The investigator will record all relevant information about any AE (including SAEs and UADEs) on the AE log. It is not acceptable for the investigator to send photocopies of the subject’s medical records in lieu of the properly completed AE or SAE log. If this request occurs, all subject identifiers and protected health information will be blinded on the copies of the medical records, before submission to the appropriate authorities.

The investigator will also attempt to report a diagnosis versus signs, symptoms, or other clinical information for the AE. The diagnosis, not the individual signs and symptoms, will be documented on the appropriate page of the AE or SAE log. In addition, SAEs need to be reported on the SAE report form.

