### Safety endpoints

The safety endpoints include:

- Subject incidence of adverse events, including changes in stool consistency assessed by Bristol scale, changes in stool amount/frequency (if applicable), increased ostomy output (if applicable, defined as >2.5 mL/kg/hour), the need to decrease enteral feeds, changes in urine color assessed by Dehydration Color scale, and discontinuation from the study treatment.
- Subject incidence of abnormalities in vital signs, assessed at baseline, Day 7, 14, 28, 60, and 90.
- Subject incidence of abnormalities in hematology and biochemistry parameters assessed at baseline, Day 7, 14, 28, 60, and 90.

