# PROCEDURES FOR HANDLING ADVERSE EVENTS AND SERIOUS ADVERSE EVENTS

## DEFINITION OF AN ADVERSE EVENT

The following definition of adverse event (AE) will be used for this study:

- Adverse event means any untoward medical occurrence associated with the use of a device in humans, whether or not considered device-related.
- All AE’s post-baseline will be captured. Adverse events grade 2 or higher will be analyzed.

An adverse event can be any unfavorable and unintended sign (including an abnormal laboratory finding), symptom, or disease (new or exacerbated) temporally associated with the use of the investigational product, regardless of whether it is considered to be related to the investigational product.

Examples of AEs include the following:

- Significant or unexpected worsening or exacerbation of the indication under study
- Exacerbation of a chronic or intermittent preexisting condition including an increase in frequency or intensity of the condition
- New conditions detected or diagnosed after investigational product administration even if they were present before the start of the study
- Signs, symptoms, or the clinical sequelae of a suspected interaction with another medical product
- Signs, symptoms or the clinical sequelae of a suspected overdose of either investigational product or a concurrent medication

Overdose will not be reported as an AE or serious adverse event (SAE), but rather the symptoms resulting from the overdose.

Examples of AEs do not include the following:

- Situations that are unwanted by the subject but in which an untoward medical occurrence did not occur, for example social inconvenience after admission to a hospital
- Anticipated day-to-day fluctuations of a preexisting disease or condition (present or detected before enrollment) that does not worsen overall
- Expected progression of the disease being studied, including signs or symptoms of the disease, unless progression is more severe than expected for the subject’s condition
- The Common Terminology Criteria for Adverse Events (CTCAE) version 5 (https://ctep.cancer.gov/protocoldevelopment/electronic_applications/docs/CTCAE_v5_Quick_Reference_5x7.pdf) will be used to grade toxicities.

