### Safety Analysis

Safety analysis will be performed on all subjects enrolled in the study with a follow-up safety assessment. Adverse event data will be listed individually and summarized by system organ class and preferred terms within a system organ class. The number and percentage of subjects with adverse events (AEs), serious adverse events (SAEs), AEs that lead to discontinuation, study device-related AEs (determined by investigator), and AEs that lead to death will be summarized. Only AEs grade 2 or higher will be presented. When calculating the incidence of adverse events, each adverse event will be counted only once for a given subject. If the same adverse event occurs on multiple occasions in a subject, the occurrence with the highest severity and relationship to study device will be reported. If two or more adverse events are reported as a unit, the individual terms will be reported as separate events. AEs will also be summarized with regards to severity and relation to study drug. Additionally, the frequency of each AE within-subject will be calculated and summarized across all subjects in order to rank the commonality of each particular AE.

Vital signs, hematology, and clinical chemistry parameters from baseline to the end of the study will be presented as outlined above for continuous outcomes and reported to the DSMB at the regularly scheduled meetings. Incidence of changes in laboratory parameters from normal to abnormal, based on Boston Children’s Hospital reference ranges, will be identified and lab values listed by subject.

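### The adverse event recording rules are not reconciled with the stool, ostomy, feed-decrease and urine-color items named in the safety endpoint, so those items may be under-counted or inconsistently counted

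*Protocol*

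**What the plan says.** **The endpoint.** Protocol section 3.3.3 (Safety endpoints) opens with: "Subject incidence of adverse events, including changes in stool consistency assessed by Bristol scale, changes in stool amount/frequency (if applicable), increased ostomy output". It sets the ostomy threshold at more than 2.5 mL/kg/hour and continues: "the need to decrease enteral feeds, changes in urine color assessed by Dehydration Color scale, and discontinuation from the study treatment". The Synopsis (safety objectives and safety outcomes) and section 2.3 repeat the list. The Synopsis ties the incidence outcome to grade 2 or higher; section 3.3.3 does not.

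**The recording rule.** Section 9.4 says: "The investigator will also attempt to report a diagnosis versus signs, symptoms, or other clinical information for the AE". The next sentence is: "The diagnosis, not the individual signs and symptoms, will be documented on the appropriate page of the AE or SAE log".

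**The exclusions.** Section 9.1 lists what is not an adverse event, including: "Expected progression of the disease being studied, including signs or symptoms of the disease, unless progression is more severe than expected"; and: "Anticipated day-to-day fluctuations of a preexisting disease or condition (present or detected before enrollment) that does not worsen overall".

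**The analysis.** Section 10.2.3 summarises adverse events by system organ class and preferred term and restricts presentation to grade 2 or higher. It adds: "If two or more adverse events are reported as a unit, the individual terms will be reported as separate events".

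**Other capture.** Caregivers record stool, ostomy output, symptoms and adverse events daily (section 6.1, including Table 2 footnote j). Table 2 also has a row for changes in PN or enteral feeding, completed at clinic visits and weekly between the later ones.

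**The concern.** Most of the named items are signs (stool, ostomy output, urine color) or management actions (decreasing feeds). The recording rule in 9.4 prefers a diagnosis to signs, and an exclusion in 9.1 concerns signs of the disease under study. In short bowel syndrome, a change in stool or ostomy output is easily read as such a sign or folded into a diagnosis such as gastroenteritis. In either case it can leave no entry under its own term.

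This matters because the trial is open-label, single-center and uncontrolled. No comparison arm is recorded under the same conventions, so incomplete recording cannot be told apart from good tolerability. The items at risk are also the gastrointestinal and hydration effects that the protocol chose to name.

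**Working it through.** The protocol gives no share of events that would be lost, so the main check sets the rules side by side. The arithmetic only shows what a given loss would mean at this sample size.

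**1. Route of each named item through the rules**

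- *Stool consistency, amount, frequency.* These are signs. Under 9.4 they can be replaced by a diagnosis. Under 9.1 they can be judged expected for the disease or a fluctuation. If logged below grade 2, they are not presented (10.2.3).
- *Ostomy output above 2.5 mL/kg/hour.* This has a numeric definition, but the same three routes apply, because no text says that crossing the threshold is itself a recorded event.
- *Need to decrease enteral feeds.* This is an action. The diagnosis rule does not clearly remove it, but no rule says when it becomes an adverse event or under what term. Table 2 records feeding changes, and no stated summary turns them into a subject incidence.
- *Urine-color change.* This is a scale reading kept in the diary. No rule converts a change into an event.
- *Discontinuation.* This is the best covered item. The reason goes to the CRF (section 9.12), and events leading to discontinuation are tabulated (10.2.3).

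**2. Search for a reconciling rule**

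No section exempts the 3.3.3 items from 9.4 or from the disease-sign exclusion. Section 10.2.2 refers adverse event incidence to 10.2.3, whose other summaries cover vital signs and laboratory values. No stated rule turns a diary entry into an endpoint count.

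**3. The plan's own precision figures**

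Inputs from section 10.2.5: n = 32 and p = 0.20, 0.50, 0.80. Formula: p ± 1.96 × √(p(1 − p)/32).

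- p = 0.20: 0.20 ± 0.139 = 0.061 to 0.339 (stated 0.06 to 0.34)
- p = 0.50: 0.50 ± 0.173 = 0.327 to 0.673 (stated 0.33 to 0.67)
- p = 0.80: 0.80 ± 0.139 = 0.661 to 0.939 (stated 0.66 to 0.94)

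All three agree.

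**4. What a loss would do**

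One child is 1/32 = 3.1 percentage points. Let s be the share of affected children whose event is logged under its own term. This is an assumption; the protocol gives no value. The expected reported incidence is p × s, with the same interval formula and a lower limit cut at 0.

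| True incidence | Assumed s | Reported | 95% interval | Covers the truth? |
|---|---|---|---|---|
| 0.50 | 0.90 | 0.45 | 0.28 to 0.62 | yes |
| 0.50 | 0.75 | 0.375 | 0.21 to 0.54 | yes |
| 0.50 | 0.50 | 0.25 | 0.10 to 0.40 | no |
| 0.80 | 0.75 | 0.60 | 0.43 to 0.77 | no |
| 0.20 | 0.50 | 0.10 | 0 to 0.204 | just |

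Modest losses stay inside the sampling error. Large losses, or moderate losses of common events, do not.

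**The case against.** There is a fair case that the protocol already captures these items. Sections 2.3 and 3.3.3 call them adverse events by name, and a specific designation can be read as overriding general text. Section 9.4 asks only for an attempt at a diagnosis. Both exclusions in 9.1 are conditional, and the same section allows a sign or symptom to be an adverse event and counts an increase in the frequency or intensity of a chronic condition. All clinical complaints go to the CRF, and caregivers record events daily. A separate tolerability table could also be left to a statistical analysis plan, which is not at hand.

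Much of this stands. It shows that clear worsening remains an adverse event and that the raw data will exist. It does not settle the conflict: section 9.1 can support either answer for the same episode, and the 9.4 sentence governs what the investigator logs during the trial, which a later analysis plan does not change.

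A reader might go further than the text allows in five ways:

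- That the endpoint consists of these items. It includes them, and there are further safety endpoints, for example: "Subject incidence of abnormalities in vital signs, assessed at baseline, Day 7, 14, 28, 60, and 90".
- That the listed items would read as zero. The conditional wording and the daily recording do not support that.
- That the AE log is the only source for the analysis. Section 10.2.3 names no exclusive source.
- That the DSMB would see the same reduced counts. Section 10.2.3 names vital signs and laboratory data for its meetings, section 9.8 sends it serious events, and section 8.0 refers other details to a charter that is not shown.
- That the rule in 10.2.3 on events reported as a unit contradicts 9.4. It concerns events logged jointly and favors capture, although it cannot restore a sign that was never logged.

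**Conclusion.** The concern holds as an unreconciled conflict between the named endpoint items (section 3.3.3, the Synopsis and section 2.3) and the rules in 9.1, 9.4 and 10.2.3. The items may be under-counted or counted inconsistently between children. Where the rules act, they remove events, so the error favors apparent tolerability. That events will in fact be under-counted is an inference that the text does not establish.

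The size cannot be computed from the protocol. The 3.1 percentage points per child assumes all 32 children in the denominator, and the losses tabulated above rest on assumed logged shares. The grade 2 restriction is a further explicit route by which milder instances go unreported.

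**What to change.** Reconcile sections 3.3.3, 9.1, 9.4 and 10.2.3 as follows.

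1. State in 9.4 that the items listed in 3.3.3 are recorded under their own terms even when a diagnosis is also logged, and cross-refer to this in 9.1.
2. Keep the day-to-day fluctuation exclusion in 9.1. Judge the listed items against each child's own baseline and, for ostomy output, against the threshold already in 3.3.3. A blanket exemption from the 9.1 exclusions would be too wide, since ordinary stool variation could then count as an event in nearly every child.
3. In 10.2.3, add a separate table of subject incidence for the listed items, taken from the daily diary and the weekly PN and enteral feeding-change record, whether or not a diagnosis was logged and without the grade 2 restriction.
4. Keep the diagnosis convention for the table by system organ class and preferred term.

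The cost is a few sentences and one table from data already collected. The reported tolerability incidence will be higher than under the present rules, and the text should say why.

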## ASSESSMENT OF INTENSITY

The investigator will assess the intensity for each AE and SAE reported during the study. The assessment will be based on the investigator’s clinical judgment.

The classifications in Table 6 will be used in assigning intensity of each AE recorded in the case report form. The Common Terminology Criteria for Adverse Events (CTCAE) version 5.0 will be used to grade toxicities. (https://ctep.cancer.gov/protocolDevelopment/electronic_applications/ctc.htm)

Table 6. Classification of AEs by Intensity

| **Intensity** ^a^ | **Definition** |
| --- | --- |
| Mild AE (Grade 1) | An event that is easily tolerated by the subject, causing minimal discomfort and not interfering with everyday activities. |
| Moderate AE (Grade 2) | An event that is sufficiently discomforting to the extent of interfering with normal everyday activities. |
| Severe AE (Grade 3) | An event that prevents the subject from performing normal everyday activities. |
| Life-threatening or disabling AE (Grade 4) | An event that, at the time of occurrence, put the subject at risk of death or resulted in a persistent or significant disability or incapacity |
| Death related to AE  (Grade 5) | An event that resulted in death |

AE = adverse event

a From Common Terminology Criteria for Adverse Events (https://ctep.cancer.gov/protocolDevelopment/electronic_applications/ctc.htm)

Any AE that changes in intensity or grade during its course will be recorded in the CRF at the highest-level experience by the subject during a single course.

An AE that is assessed as severe should not be confused with an SAE. Severity is a category used for rating the intensity of an AE (such as mild, moderate, or severe myocardial infarction). However, the event itself may be of relatively minor medical significance, such as a severe headache. Both AEs and SAEs can be assessed as severe. An AE is defined as serious when it meets one of the pre‑defined outcomes as described in Section 9.2.

## ASSESSMENT OF CAUSALITY

The investigator must estimate the relationship between the investigational product and the occurrence of each AE or SAE by using his or her best clinical judgment. Elements to consider for this estimate include the history of the underlying disease, concomitant therapy, other risk factors, and the temporal relationship of the event to the investigational product. Because of reporting timelines, the investigator might have minimal information to include in the initial SAE report. However, the investigator must always make an assessment of causality for every event before the transmission of the SAE report. The investigator may change his or her opinion of the causality in light of follow-up information, with subsequent amendment of the SAE report. Causality assessment is one of the criteria used to determine regulatory reporting requirements and should not be left blank. Table 7 provides some definitions to use in the assessment.

Table 7. Assessment of Causality of AEs

| **Term** | **Definition** |
| --- | --- |
| **Definitely related** | The AE is clearly related to the investigational agent(s) or research intervention: the AE has a temporal relationship to the administration of the investigational agent(s) or research intervention and follows a known pattern of response, and no alternative cause is present. |
| **Possibly related** | The AE may be related to the investigational agent(s) or intervention: the AE has a temporal relationship to the administration of the investigational agent(s) or research intervention and follows a suspected pattern of response, but an alternative cause is present. |
| **Probably related** | The AE is likely related to the investigational agent(s) or intervention: the AE has a temporal relationship to the administration of the investigational agent(s) or research intervention and follows a known or suspected pattern of response, but an alternative cause may be present. |
| **Unrelated**  **(or Not Related)** | The AE is clearly not related to the investigational agent(s) or intervention: the AE has no temporal relationship to the administration of the investigational agent(s) or research intervention, and follows no known or suspected pattern of response, and an alternative cause is present. |

AE = adverse event.

## EXPECTEDNESS OF SERIOUS ADVERSE EVENTS

An expected AE is one that is consistent with the known risk information described in the product label (if applicable) or the current Investigator’s Brochure. The assessment of the expectedness of an SAE will be done by the Principal Investigator, upon receipt of the initial SAE report.

## REPORTING OF SERIOUS ADVERSE EVENTS

Any SAE occurring after use of the study device must be reported to the IRB and the Data and Safety Monitoring Board (DSMB) by phone or in person within 72 hours of the time the investigator becomes aware of the SAE, or within 24 hours if the event is fatal or life threatening. Urgent reporting of SAEs is required for the following reasons:

1. To enable the Investigational Product developer/distributer to fulfill the reporting requirements to the appropriate regulatory authority
2. To facilitate discussion between the Investigational Product developer/distributer and the sponsor-investigator about appropriate follow-up measures (if necessary)
3. To facilitate reporting unanticipated problems involving risk to subjects to the institutional review board (IRB) or independent ethics committee (IEC)

The SAE report form will be completed as thoroughly as possible, including:

- Subject identification information
- All available details about the event
- Causality of each SAE
- Signature of the investigator

The SAE report form will be forwarded to the safety department within the designated time frames. If additional information to complete the SAE report form is needed, the investigator will not wait before notifying the safety department of the SAE. The SAE report form will be updated by the investigator when additional information is received.

SAEs and UADEs will be reported to the FDA in accordance with FDA reporting requirements.

## FOLLOW-UP OF ADVERSE EVENTS AND SERIOUS ADVERSE EVENTS

After the initial AE or SAE report, the investigator is required to proactively follow each subject and provide further information to the safety group about the subject’s condition.

All AEs and SAEs will be followed until the occurrence of one of the following:

- Resolution
- The condition stabilizes
- The event is otherwise explained
- The subject is lost to follow-up

The appropriate SAE report form will be updated once the SAE resolves, stabilizes, is otherwise explained, or the subject is lost to follow-up. The investigator will also ensure that updates include any supplemental data that may explain causality of the event(s).

New or updated information will be recorded on a copy of the initial SAE report form, with all the changes signed and dated by the investigator or designee. The updated SAE report form will then be signed by the investigator and resubmitted to the safety department.

## LIVER EVENTS

When either serum alanine aminotransferase (ALT) or serum aspartate aminotransferase (AST) levels exceed three times higher than values recorded at screening, serum ALT, AST, alkaline phosphatase, and total bilirubin will be repeated within 48 to 72 hours. Alcresta will be notified, and liver event pages of the case report form will be completed. If the ALT or AST remain more than three times the values recorded at screening, or total bilirubin remains greater than two times ULN, then repeat liver enzymes will be obtained every 3 days and the appropriate case report form page will be completed with available history of symptoms and other assessments (e.g., ultrasound or computerized tomography of the liver and tests for hepatitis).

Investigational product use will stop if one of the following occurs:

- ALT or AST exceed eight times the values recorded at screening.
- ALT or AST exceed five times the values recorded at screening for more than 2 weeks.
- ALT or AST exceed three times the values recorded at screening and total bilirubin exceeds two times ULN or international normalized ratio exceeds 1.5.
- ALT or AST exceed three times the values recorded at screening, with the appearance of fatigue, nausea, vomiting, right upper quadrant pain or tenderness, fever, rash, or eosinophilia (>5%).
- Monitoring will be continued until abnormalities return to reference range or baseline levels.

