| **Experimental procedures:**  **Screening Period (Day -3)**  The following evaluations will be performed to assess the subject’s eligibility for the study:   - Complete medical history - Vital signs   - Temperature, blood pressure, pulse rate, and respiratory rate - Clinical lab evaluations   - Chemistry (sodium, potassium, chloride, CO2, glucose, blood urea nitrogen (BUN), creatinine, calcium, phosphorus, magnesium, alkaline phosphatase, albumin, pre-albumin, total protein, total and direct bilirubin, triglycerides)   - Lipid profile (i.e. cholesterol, high-density lipoprotein (HDL), very low-density lipoprotein (VLDL), low-density lipoprotein (LDL))   - Serum C-reactive protein (CRP), fatty acid profile | |
| - Nutritional intake   - Oral and enteral intake and PN volume intake   - Stool consistency (Bristol scale)/amount/volume (if applicable)   - Ostomy (if applicable) output | |
|  | |
| - Liver enzymes   - Serum alanine aminotransferase (ALT)   - Serum aspartate aminotransferase (AST)   - Serum gamma-glutamyl transpeptidase (GGT)   Results from screening must not show any clinically significant abnormalities in order for the subject to be enrolled and progress to the treatment phase of the trial. | |
| **Enrollment (Day -3 to -1) and First Day of Treatment (Day 1)**  Assessments of safety and clinical status will include:   - Vital signs (temperature, blood pressure, pulse rate, and respiratory rate) - Physical examination - Height or length, head circumference (for subjects < 36 months), and weight. - NOTE: physical examinations performed during the screening period will be used for the baseline assessment when available.   Assessments of clinical endpoints will include:   - 72-hour fecal collection for total fat and fatty acid analysis - Lipid profile (i.e., cholesterol, high-density lipoprotein (HDL), very low-density lipoprotein (VLDL), low-density lipoprotein (LDL) - Fat-soluble vitamins (A, D, E, and K) - Liver Tests (AST, ALT, GGT) - Total plasma fatty acids - total saturated, total monosaturated, total polyunsaturated, total Omega 3, total Omega 6, total fatty acids - a-linolenic Acid, linoleic acid, oleic acid, EPA, arachidonic acid, mead acid, DHA, triene:tetraene ratio - Nutritional intake - Daily caloric intake of enteral fat and PO as well as PN volume will be documented | |

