| Clinical laboratory evaluations^d^ | X |  |  |  | X |  | X |  | X |
| Dietician Education | X |  | X |  | X |  | X |  | X |
| 72-hour fecal collection^e^ |  | X |  |  |  |  |  |  | X (final visit) |
| Lipid profile^f^ | X |  |  |  | X |  | X |  | X |
| Total plasma FAs^g^ | X |  |  |  | X |  | X |  | X |
| Liver tests^h^ | X |  |  |  | X |  | X |  | X |
| Nutritional assessment | X |  | X |  | X |  | X | Weekly | X |
| Record nutritional intake^i^ |  | Daily | X | Daily | X | Daily | X | Daily | X |
| Change in PN/ enteral feeding | X | X | X |  | X |  | X | Weekly | X |
| Home Body weight (WAZ) |  |  |  |  |  |  |  | Weekly |  |
| RELiZORB |  |  | X | Daily | X | Daily | X | Daily | X |
| Adverse Events^j^ |  |  | X | Daily | X | Daily | X | Daily | X |
| Concomitant Medications |  |  | X | Daily | X | Daily | X | Daily | X |
| Assess medical/ surgical procedures | X |  | X |  |  |  | X |  | X |
| Supply Investigational Product |  |  | X |  | X |  | X |  | X |
| Review Daily Patient Diary |  |  |  |  | X |  | X | Weekly | X |

I/E criteria = Inclusion and exclusion criteria.

FAs =fatty acids.

PN = Parenteral nutrition.

^a^ Record known bowel length/type from last surgical resection or other measurement.

^b^ Blood pressure, pulse rate, respiratory rate and temperature.

^c^ Includes height or length, head circumference (for subjects < 36 months), and weight. If a physical examination or nutrition assessment was performed during the 3-day screening period, it will be used for the baseline assessment when available.

^d^ Includes chemistry (including fat-soluble Vitamins A, D, E, and K), hematology, coagulation and C-reactive protein (CRP). Clinical laboratory evaluations obtained at time of screening will serve as the baseline assessment.

^e^ 72-hour fecal collection will occur in the 72 hours preceding treatment day 1 and the final clinic visit day 90

^f^ Samples of the lipid profile will include cholesterol, high-density lipoprotein (HDL), very low-density lipoprotein (VLDL), and low-density lipoprotein (LDL). Results of samples obtained at time of screening will be analyzed during enrollment period, prior to participant receiving device.

^g^ Samples of total plasma fatty acids will include total saturated, total monosaturated, total polyunsaturated, total Omega-3, total Omega 6, total fatty acids, a-linolenic Acid, linoleic acid, oleic acid, EPA, arachidonic acid, mead acid, DHA, and triene:tetraene ratio.

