^h^ Serum alanine aminotransferase (ALT), serum aspartate aminotransferase (AST), and serum gamma-glutamyl transpeptidase (GGT)

^i^ 24-hour nutritional intake/composition (PO and enteral dietary intake and PN volume) will be recorded using a phone-based application or paper diary. This will be especially important during the 72-hour stool collection periods for calculation of the coefficient of fat absorption.

^j^ Adverse events will be recorded daily in an electronic or paper format by the subject’s parent or guardian, and by study staff during clinic visits. Monitoring of these events will also occur through a daily phone call from a study coordinator. If any AEs or concerns are noted by the family, the study coordinator will alert the study team by email. PI or other delegated investigator will determine next steps

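### The liver stopping rules in Section 9.10 use INR and eosinophils, but the follow-up tests it prescribes between clinic visits include neither

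*Protocol*

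**What the plan says.** Section 9.10 (Liver Events) sets a follow-up sequence and then a list of stopping criteria.

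Follow-up starts when ALT or AST exceeds three times its screening value: "serum ALT, AST, alkaline phosphatase, and total bilirubin will be repeated within 48 to 72 hours". If ALT or AST stays above that level, or total bilirubin stays above two times ULN, "then repeat liver enzymes will be obtained every 3 days".

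Device use must stop on any of four criteria:

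1. "ALT or AST exceed eight times the values recorded at screening".
2. "ALT or AST exceed five times the values recorded at screening for more than 2 weeks".
3. "ALT or AST exceed three times the values recorded at screening and total bilirubin exceeds two times ULN or international normalized ratio exceeds 1.5".
4. ALT or AST above three times screening together with any of several listed symptoms or signs, or eosinophilia above 5%.

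A fifth bullet is a statement about continued monitoring, not a stopping criterion. It names no analytes and no interval.

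Outside Section 9.10, coagulation and hematology belong to the clinical laboratory evaluations in Table 2, whose footnote d reads "Includes chemistry (including fat-soluble Vitamins A, D, E, and K), hematology, coagulation and C-reactive protein (CRP". Table 2 schedules that panel at screening and on Days 7, 14, 28, 60 and 90. Footnote h describes the liver tests as "Serum alanine aminotransferase (ALT), serum aspartate aminotransferase (AST), and serum gamma-glutamyl transpeptidase (GGT".

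**The concern.** The repeat draws exist to show whether a child with raised transaminases is moving towards a mandatory stop. Two of the four criteria depend partly on results that those draws are not asked to produce. INR decides one arm of criterion 3 and eosinophils one arm of criterion 4, and neither is in the 48 to 72 hour repeat or the every-3-day repeats. If followed literally, the plan has a rule that says use will stop but no prescribed measurement to invoke those arms between visits.

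The children are dependent on parenteral nutrition, and Section 1.1 describes hepatic and biliary disorders as the most frequent of the serious metabolic complications of long-term parenteral nutrition. A stopping rule that cannot be fully applied during follow-up is therefore worth correcting, however rarely it is triggered.

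**Working it through.** No power or alpha figure is involved. The check sets what each criterion needs against what is prescribed at each step, then measures the gap between scheduled visits.

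**Analytes needed and analytes ordered**

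| Stop criterion (9.10) | Needs | Clinic visit (Table 2) | 48–72 h repeat | Every-3-day repeats |
|---|---|---|---|---|
| 1. Above 8× screening | ALT/AST | yes | yes | yes |
| 2. Above 5× for over 2 weeks | ALT/AST over time | yes | yes | yes |
| 3. Above 3× with bilirubin or INR | bilirubin or INR | yes* | bilirubin arm only | no INR; bilirubin unclear |
| 4. Above 3× with symptoms or eosinophilia | symptoms or eosinophils | yes* | symptom arm only | symptom arm only |

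*Assumes that the coagulation panel includes INR and the hematology panel includes a differential. The protocol spells out neither.

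Criterion 3 is read here as ALT or AST above three times screening together with either bilirubin or INR. On that reading all four criteria are assessable at a clinic visit, and two of four are fully assessable at either kind of repeat.

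**What liver enzymes covers**

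The passages point two ways.

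- The synopsis screening list puts ALT, AST and "Serum gamma-glutamyl transpeptidase (GGT" under liver enzymes and places bilirubin under chemistry. Footnote h of Table 2 gives the same three analytes for liver tests. On this usage bilirubin is not measured at the 3-day repeats.
- In Section 9.10 itself, bilirubin persisting above two times ULN is one of the triggers for those repeats. The repeat just before them included bilirubin and alkaline phosphatase and left out GGT. On this usage the phrase may mean the panel already listed.

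The text does not settle which is meant.

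**How long the gap can last**

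Inputs: clinic visits on Days 7, 14, 28, 60 and 90, each ±3 days (synopsis, Methodology; Table 2).

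- Nominal gaps: 14 − 7 = 7; 28 − 14 = 14; 60 − 28 = 32; 90 − 60 = 30 days.
- Longest gaps with windows: (60 + 3) − (28 − 3) = 38 and (90 + 3) − (60 − 3) = 36 days.

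For a child whose Day 28 sample triggers the rule (ignoring laboratory turnaround), with the first repeat on Day 30 or 31:

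- The 3-day series runs on Days 33, 36, …, 57 or Days 34, 37, …, 58, which is 9 draws before Day 60.
- At the window extremes (trigger on Day 25, next visit on Day 63, first repeat on Day 27 or 28) it runs on Days 30, …, 60 or Days 31, …, 61, which is 11 draws.

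Counting the first repeat, 10 to 12 draws could pass with no prescribed INR or eosinophil result. This is an upper figure for a child whose values keep the series going and who meets no other stop criterion.

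**The case against.** Several points count against giving this more weight.

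- **The triggering sample is covered.** Scheduled ALT and AST are drawn at clinic visits, where chemistry, coagulation and hematology are also scheduled. All four criteria can normally be checked at that moment. This stands, and it confines the gap to abnormalities that emerge afterwards.
- **Other safeguards remain active.** Criteria 1 and 2 can be applied at every repeat, and symptoms are followed through daily diaries and coordinator calls. Unscheduled visits are possible (Sections 3.1 and 7.1.4), adverse events are followed to resolution or stabilisation (Section 9.9), and a subject may be discontinued for unacceptable risk (Section 9.12.1). The listed tests are a minimum and an investigator may add to them. This also stands. A reader might infer that a child who meets the rule necessarily stays on the device until the next visit, and these provisions do not support that. None of them, however, prescribes INR or eosinophils.
- **Bilirubin may well continue.** A reader might infer from the synopsis list that bilirubin is dropped after the first repeat. Section 9.10's own use of bilirubin as a trigger makes that uncertain, so only the ambiguity can be asserted.
- **The synopsis list is not a gap in testing.** Its screening list names neither coagulation nor hematology, but Section 7.1.1 and Table 2 footnote d name both. That difference is clerical.
- **The liver risk is not attributed to the device.** Section 1.1 links it to long-term parenteral nutrition, and Section 1.2 reports a nonsignificant-risk determination. The protocol gives no expected frequency of transaminase rises above three times screening, so the number of children affected cannot be estimated.

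**Conclusion.** The point holds in a limited form. Section 9.10 ties mandatory stopping to INR and eosinophils, yet its own follow-up sequence never orders either, and it leaves open whether bilirubin is measured after the first repeat. Two of four criteria are therefore only partly assessable at the repeats. An INR or eosinophil criterion that emerges after the triggering visit would go undetected by the prescribed tests until the next clinic visit, nominally up to 32 days later and up to 38 with the windows.

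This assumes that coagulation includes INR, that hematology includes a differential, and that no extra test is ordered at the investigator's discretion. The INR and eosinophil part needs no interpretation of the text; the bilirubin part is a question of wording. The matter should be corrected because it concerns patient safety and is cheap to resolve. It does not show that the liver rule as a whole is inoperable.

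**What to change.** The sponsor-investigator should reconcile the repeat-test list in Section 9.10 with the analytes on which its stop criteria depend, so that each criterion can be applied from what the section prescribes. The section should also state which analytes liver enzymes covers at the every-3-day repeats. Which passage changes, and in which direction, is the sponsor-investigator's clinical decision, as are the thresholds.

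The cost is a wording change. If tests are added as a result, it also means a few more assays and slightly more blood at draws already being taken, only in children who trigger the rule.
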